**Figure 1. F1:**
[figure not shown]
A simplified outline of the study protocol based on the CONSORT (Consolidated Standards of Reporting Trials) diagram. CAL: clinical attachment loss; i-PRF: injectable platelet-rich fibrin; PBI: papillary bleeding index; PD: probing depth; PI: plaque index.

### Recruitment

Patients in the Outpatient Department of Periodontics and Implantology, Sharad Pawar Dental College and Hospital, Sawangi (Meghe), Wardha, were recruited.

### Randomization and Masking

The eligible patients will be randomly assigned to either test group (i-PRF as an adjuvant in OS-FMD) or the control group (OS-FMD alone) in patients with stage II and III periodontitis. All participants will undergo a periodontal health assessment via clinical examination. Informed consent will be obtained from all participants in written format following a thorough explanation of the nature, purpose, potential benefits, and risks of the intervention. Along with obtaining informed consent, a complete and detailed medical history will also be obtained from the patients after receiving a thorough explanation of the proposed intervention.

Central randomization will be carried out for this study by using a secure computerized system, with assigning a unique study code to each participant, in order to ensure confidentiality. Data presented to the operators and research evaluators will be anonymized and presented using this coded format. During the phase of data analysis, the statistician will remain blinded to group allocation to minimize bias and enhance the objectivity and reliability of the results.

### Clinical Procedure

Information concerning dietary habits, systemic health status, oral hygiene practices, and gingival and periodontal conditions, and other routine clinical parameters, will be documented in the specially designed clinical chart, along with obtaining thorough medical and past dental history from the patients. Clinical examination of the patients will be performed under adequate illumination using a mouth mirror and a UNC-15 periodontal probe.

### Test Group

In the test group, patients will receive OS-FMD 1 week after the completion of supragingival scaling to allow for initial plaque control and gingival stabilization. Under local anesthesia, full-mouth subgingival SRP will be performed using an ultrasonic scaler and curettes, respectively, within 24 hours. Mechanical debridement will be complemented by the application of chlorhexidine to disinfect the intraoral niches.

The patient will be instructed to brush the dorsum of the tongue with 1% chlorhexidine gel for 1 minute, immediately following each instrumentation session. Tongue cleaning will be followed by rinsing with 0.2% chlorhexidine solution 2 times, each lasting for a minute. The pharyngeal region will then be sprayed with 0.2% chlorhexidine spray, followed by irrigation of all the periodontal pockets with 0.2% chlorhexidine solution thrice, within 10 minutes. Additionally, the prescription to use 0.2% chlorhexidine mouthwash twice daily will be given to the patient for 1 week following FMD [14]. One week postoperatively, i-PRF will be administered subgingivally into all periodontal pockets.

### Preparation of I-PRF

The preparation of i-PRF will be conducted in a sterile environment with careful handling to maintain biosafety. Blood will be withdrawn only once per patient in the test group**,** with no repeated phlebotomy, thereby minimizing participant discomfort and procedural risks. All phlebotomy procedures will be performed by trained personnel under strict aseptic conditions using sterile, disposable equipment to minimize infection risk. Participants will be closely monitored during and after venipuncture, and standard protocols for managing potential complications such as hematoma, vasovagal episodes, or allergic reactions will be in place. In case of emergency, immediate medical management will be carried out and referral, if necessary, and the case will be reported to the Data Monitoring Committee (DMC) and the Institutional Ethics Committee (IEC) according to the severity of adverse events (AEs).

10 ml of venous blood will be drawn immediately, just before subgingival administration, through antecubital venipuncture under strict aseptic conditions. i-PRF is a second-generation platelet concentrate, which is a blood-derived autologous biomaterial that possesses a 3D fibrin network, while maintaining its fluid consistency [15]. The obtained blood without the use of anticoagulants is then transferred into a sterile glass test tube. The whole blood will be subjected to low-speed centrifugation at 700 rpm (60×g) at room temperature for 3 minutes using the Dental Laboratory Centrifuge by Labtech Disposables. The low-speed centrifugation technique allows the separation of the components of blood, allowing the formation of the upper layer of liquid, which is rich in fibrinogen and growth factors, collected as i-PRF. In contrast to PRP, which requires multiple centrifugation steps and the addition of anticoagulants, for i-PRF, a single spin is required without the use of anticoagulants. This allows preservation of higher concentrations of growth factors and regenerative cells, enhancing its efficacy in the promotion of tissue regeneration and healing [12].

### Control Group

In the control group, patients will receive OS-FMD 1 week after the completion of supragingival scaling. Under local anesthesia, full-mouth subgingival SRP will be performed using an ultrasonic scaler and curettes, respectively, within 24 hours. Mechanical debridement will be complemented by the application of chlorhexidine to disinfect the intra-oral niches.

The patient will be instructed to brush the dorsum of the tongue with 1% chlorhexidine gel for 1 minute, immediately following each instrumentation session. Tongue cleaning will be followed by rinsing with 0.2% chlorhexidine solution 2 times, each lasting for a minute. The pharyngeal region will then be sprayed with 0.2% chlorhexidine spray, followed by irrigation of all the periodontal pockets with 0.2% chlorhexidine solution thrice, within 10 minutes. Additionally, the prescription to use 0.2% chlorhexidine mouthwash twice daily will be given to the patient for 1 week following FMD [14].

### Clinical Measurements

#### Clinical Indices

In order to ensure consistency, reduce interoperator variability, and minimize bias, all clinical recordings will be performed by the same calibrated examiner who is blinded to group allocation. The mean values of these indices will be calculated for outcome assessment.

The status of oral hygiene will be evaluated using the Full Mouth Plaque Index, based on the Turesky-Gilmore-Glickman modification of the Quigley Hein Index (1970) by which assessment of plaque will be carried out on the buccal or labial and lingual surfaces of all teeth after application of a disclosing agent [16].

For the measurement of gingival inflammation, the full-mouth PBI by Rebelo and Queiroz [13] will be recorded. Recordings will be obtained by carefully inserting the periodontal probe into the gingival sulcus at the base of the papilla on the mesial aspect, then gently moving it coronally toward the tip of the papilla. The procedure will be repeated on the distal aspect of the same papilla. The intensity of bleeding provoked by probing will be assessed using a standardized scale ranging from 0 to 4 to evaluate gingival inflammation [16].

#### Probing Measurements

To evaluate treatment outcomes, clinical parameters will be assessed using the UNC-15 probe (Hu-Friedy) to measure PD and CAL. For recording probing measurements, the deepest probing site will be evaluated and recorded. Measurements will be taken at baseline, and subsequently at 3 and 6 months.

### Statistical Analysis

The values of mean (SD) will be calculated for each of the clinical periodontal parameters, including PI, PBI, PD, and CAL. To assess the significance of observed differences using standard methods, statistical analysis will be performed. To compare baseline values of the findings to those values at 6 months within both groups, the Wilcoxon signed-rank test will be used. Comparisons of PI, PBI, CAL, and PD will be made at baseline, after 3 months of therapy, and then after 6 months. A *P* value less than .05 will be considered statistically significant, while a *P* value greater than .05 will be considered statistically nonsignificant.

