**Methods:**

This randomized clinical trial will include 26 systemically healthy patients diagnosed with stage II and III periodontitis, selected from the Outpatient Department of Periodontics at Sharad Pawar Dental College, Sawangi (Meghe), Wardha. Participants will be randomly assigned to one of 2 groups using a parallel-arm design to ensure unbiased allocation. The control group will undergo OS-FMD therapy involving subgingival scaling and root planing for the entire dentition, which will be performed within 24 hours, supplemented by application of chlorhexidine intraorally, including mouth rinsing, pocket irrigation, and tongue cleansing. The test group will receive the same OS-FMD protocol as the control group, in addition to subgingival delivery of i-PRF in all periodontal pockets 1 week post therapy. Assessment of clinical parameters, including PI, PBI, PD, and CAL, will be done at baseline, 3 months, and 6 months. To evaluate intragroup and intergroup differences, statistical analysis will be conducted using appropriate methods, including the Wilcoxon signed-rank test. A *P* value <.05 will be considered statistically significant.

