### Primary Objectives

To evaluate and compare the outcomes of i-PRF as an adjuvant in OS-FMD and OS-FMD therapy alone by assessment of clinical parameters in patients with stage II and stage III periodontitis after 3 and 6 months in terms of reduction in PD and gain in CAL.

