## Methods

### Trial Design

This study is designed as a randomized controlled prospective parallel-arm clinical trial to enable a direct comparison between the clinical outcomes of i-PRF as an adjuvant in OS-FMD therapy and OS-FMD therapy alone in patients with stage II and III periodontitis.

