### Sample Size Calculation

The formula used for sample size calculation will be n ≥[(Z_(1-α/2)+Z_(1-β))² * (σ₁²+σ₂²/r)] / (μ₁-μ₂)², with given values: Z_(1-α/2) for a 2-tailed 95% confidence level=1.96 and Z_(1-β) for 99% power=2.33, where mean (μ1) and SD (σ1) in group 1 will be 4.36 and 0.87 respectively, mean (μ2) and SD (σ2) in group 2 will be 3.04 and 0.66 respectively, and ratio (r)=1. The required sample size is 13 participants per group (n=13).

The sample size was determined on the basis of earlier studies involving the evaluation of clinical parameters in OS-FMD therapy. Considering the outcome variable of PD and the mean difference reported in existing literature, a sample size of 26 participants in total (13 participants per group) was considered to be adequate to achieve sufficient statistical power [6].

To uphold the scientific validity of the study, the sample size was increased to 15 participants per group. This decision was made in anticipation of potential dropouts due to unforeseen reasons or noncompliance from the side of patients with follow-up protocols. By adopting this adjusted sample size, the study aims to preserve adequate statistical power, ensuring the reliability and integrity of the final outcomes, even in the event of participant loss (Figure 1).

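### The only test named, the paired Wilcoxon signed-rank test, does not match the between-arm primary objective, and no unpaired comparison is specified

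*Protocol article*

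**What the plan says.** - **Primary Objectives:** "To evaluate and compare the outcomes of i-PRF as an adjuvant in OS-FMD and OS-FMD therapy alone by assessment of clinical parameters", in terms of PD reduction and CAL gain after 3 and 6 months.
- **Trial Design:** a "randomized controlled prospective parallel-arm clinical trial to enable a direct comparison" of the two treatments. The arms contain different patients, and nothing matches a test patient to a control patient.
- **Sample Size Calculation:** a formula for two independent means, with PD as the outcome variable and a critical value "for a 2-tailed 95% confidence level=1.96".
- **Statistical Analysis:** "To compare baseline values of the findings to those values at 6 months within both groups, the Wilcoxon signed-rank test will be used". The rest is general: "To assess the significance of observed differences using standard methods, statistical analysis will be performed", and "Comparisons of PI, PBI, CAL, and PD will be made at baseline, after 3 months of therapy, and then after 6 months". The last sentence names neither a test nor the arms.
- **Abstract, Methods:** "To evaluate intragroup and intergroup differences, statistical analysis will be conducted using appropriate methods, including the Wilcoxon signed-rank test".

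**The concern.** The signed-rank test works on paired differences. It suits baseline against 6 months in the same patient, but not two groups of unrelated patients. The article gives its single named test to the within-arm contrast, and the Abstract then lists that test in a sentence that also covers the between-arm contrast. The question the trial was randomised and sized to answer has no suitable test attached to it. The named contrast also leaves out 3 months, which is part of the primary objective.

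Two things are at stake. First, a before-after test in either arm mostly measures the effect of scaling, root planing and chlorhexidine, which both arms receive. If one arm reaches P<.05 and the other does not, a reader may take that as an i-PRF effect although the arms were never compared. Second, a between-arm method left open in the published plan may end up being chosen with the data in hand.

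**Working it through.** **1. Question and method side by side**

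| Element | Comparison implied |
|---|---|
| Primary objective | Between arms; PD and CAL; 3 and 6 months |
| Design | Parallel arms, independent patients |
| Sample size formula | Between arms, two independent means |
| Test in Statistical Analysis | Within arm, paired, baseline to 6 months |
| Test in Abstract | The same paired test, for intragroup and intergroup differences |

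The first three rows agree with one another. The last two do not fit them.

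**2. The article's own sample size**

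Inputs from Sample Size Calculation: Z values 1.96 and 2.33; group 1 mean 4.36, SD 0.87; group 2 mean 3.04, SD 0.66; ratio 1. The difference is 4.36 − 3.04 = 1.32.

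n = (1.96 + 2.33)² × (0.87² + 0.66²) / 1.32² = 12.60, rounded up to 13 per group.

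The stated figure reproduces. It is the number for an unpaired comparison, which the named test does not perform.

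**3. What within-arm tests show when i-PRF adds nothing**

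The article gives no SD of change, so 0.6 to 1.0 mm is assumed. Patient-level changes are simulated as normal, with the same true mean improvement in both arms and 13 patients per arm. Each arm is tested by a two-sided signed-rank test at .05. If q is the chance that one arm is significant, both arms are significant with probability q², and exactly one with probability 2q(1−q).

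| True improvement, both arms | SD of change | q | Both significant | Exactly one significant |
|---|---|---|---|---|
| 0.5 mm | 0.6 | 0.77 | 59% | 36% |
| 0.5 mm | 0.8 | 0.52 | 27% | 50% |
| 0.5 mm | 1.0 | 0.36 | 13% | 46% |
| 1.0 mm | 0.6 | >0.99 | >99% | <1% |
| 1.0 mm | 0.8 | 0.98 | 96% | 4% |
| 1.0 mm | 1.0 | 0.90 | 80% | 19% |
| 1.3 mm | 0.6 | 1.00 | 100% | 0% |
| 1.3 mm | 0.8 | >0.99 | >99% | <1% |
| 1.3 mm | 1.0 | 0.99 | 97% | 3% |

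With a large common improvement, both arms are significant and nothing is learned about i-PRF. With a small one, a split result is common although the arms do not differ.

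**4. Whether an unpaired test needs more patients**

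On the article's means and SDs, the normal-approximation power is 99.2% at 13 per arm and 99.7% at 15. Simulated Mann-Whitney power is about 98% at 13 and 99% at 15, with a type I error of about 4.7%. The planned number is enough on those inputs.

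**The case against.** **The intention to compare arms is stated.** The Abstract refers to appropriate methods that include the signed-rank test, so the list is not closed. Statistical Analysis ties that test to within-group change, so the kindest reading of the Abstract is that the test serves only the intragroup part. The sample size formula also shows that an unpaired comparison was in mind. This stands. A reader might infer that the trial has no valid analysis or cannot answer its own question; the documents do not support that. What they show is that no valid between-arm test is specified and that the one named test is attached to the wrong contrast.

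**A condensed article may leave the test to the full protocol or analysis plan.** This stands in part. Silence on detail would be no finding. Here the article does make a choice, in its own Statistical Analysis section and in its Abstract, and that choice does not match its objective.

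**The error rates depend on assumptions.** This stands too. The split-result figure of 36% to 50% needs a true improvement of only 0.5 mm. At 1.0 to 1.3 mm it is about 0% to 4% with an SD of 0.8 mm, and up to about 19% with an SD of 1.0 mm. It is tempting to set the 50% against the nominal 5% as a false-positive rate. The article nowhere makes significance in one arm only its decision rule, so the figure is a risk of misreading and not the trial's type I error.

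**A signed-rank test between arms is not necessarily invalid.** If patients were paired without regard to outcome, simulation at 13 per arm gives a type I error of about 5% and power of about 97% on the article's inputs. The result would still depend on an arbitrary pairing. The article does not say that patients will be paired across arms, so no claim is made that it would do this.

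**Conclusion.** The analysis is wrong as written and should be corrected before the data are analysed. The single named test is paired and assigned to within-arm change from baseline to 6 months, while the objective, design and sample size all call for an unpaired comparison. No unpaired test is specified for PD or CAL at either visit.

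The mismatch itself rests on the text alone. Its size rests on an assumed SD of change of 0.6 to 1.0 mm, normal changes, 13 patients per arm and no i-PRF effect, with the results tabulated above. The conclusion that no more patients are needed rests on the article's assumed difference of 1.32 and its SDs; whether that difference is realistic is a separate matter.

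**What to change.** In Statistical Analysis, replace the sentence on the signed-rank test with wording such as:

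> The primary inference compares the two arms on patient-level PD and CAL at 3 and 6 months by ANCOVA, adjusted for the baseline value of the same variable. The adjusted mean difference is reported with its 95% confidence interval. A Mann-Whitney test on change from baseline is the sensitivity analysis. PI and PBI are analysed in the same way as secondary outcomes. Wilcoxon signed-rank tests within each arm are descriptive only and are not used to infer a difference between arms.

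In the Abstract, attach the signed-rank test to intragroup comparisons only and name the between-arm method for intergroup differences.

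This wording keeps both variables and both visits of the primary objective. Adjustment for periodontitis stage is optional with 13 to 15 patients per arm.

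The cost is a change of wording in two places. Baseline values are already collected and the sample size stays as it is. The article schedules assessments and analyses to finish by the end of 2026, so the correction should be recorded before the outcome data are examined.

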### Ethical Considerations

Ethical approval for the study is obtained from the IEC (reference number DMIHER(DU)/IEC/2025/751) of Datta Meghe Institute of Higher Education and Research (deemed to be a university). The trial has been registered prospectively with the Clinical Trials Registry of India (CTRI registration no CTRI/2025/06/088718). All the participants will be provided with the sheet consisting of information regarding the purpose, process involved, and specifications of the study. The queries of participants will be addressed, if any. Informed consent in written format will be obtained from the participants before starting this trial. Written informed consent will be obtained from the patients for the publication of their data. The participants are free to withdraw at any time during the study. Clinical assessment will be done by taking aseptic precautions into consideration, without any harm to the patient. Collection of blood sample, transferring it into a glass test tube, and preparation of i-PRF will be done with aseptic precautions and expertise without any harm to the patient. The privacy and confidentiality will be protected by deidentifying the study data. Participants will not receive any compensation for their participation in this study.

## Results

The study received approval from the IEC in June 2025. Enrollment of participants began in September 2025 and will last up to March 2026. The study is scheduled to conclude by the end of 2026 after assessments and analyses. The accessibility of the study results is anticipated in early 2027. The results of this study will highlight the therapeutic efficacy of i-PRF as an adjunct to OS-FMD therapy, evaluated on the basis of clinical parameters including PI, PBI, PD, and CAL.

The dissemination plans for the study results are via multiple channels, including research reports, peer-reviewed publications, and presentations at national and international conferences. A primary paper, focusing on the outcomes aligned with the study objectives, will be submitted to a peer-reviewed journal with a high impact factor for publication.

## Discussion

### Anticipated Findings

Periodontal therapy plays a vital role in the prevention of progression of disease and inflammation of the gingiva and supporting periodontal structures, including the periodontal ligament and alveolar bone. If the condition is left untreated, it can cause progressive attachment loss, resorption of alveolar bone, tooth mobility, and ultimately loss of the tooth. The primary aim of periodontal therapy is to stop the disease from progressing by eliminating microbial load in the form of biofilm or calculus, controlling inflammation, and restoring periodontal health through nonsurgical therapy initially and surgical interventions further, if required. OS-FMD provides a comprehensive approach by treating the entire oral cavity within 24 hours, targeting not only periodontal pockets but also other oral niches in order to prevent cross-contamination and reinfection. The OS-FMD results in a reduction of the overall treatment time and microbial load more efficiently than conventional quadrant-wise therapy. The therapy leads to enhancement of patient compliance, limits the recolonization of pathogens between treated and untreated sites, and serves as an economical option. Over 2 decades of research have shown that FMD can achieve clinical outcomes comparable to or better than conventional approaches, especially when tailored with adjunctive therapies. Chlorhexidine was most effective as an adjuvant, especially when combined with FMD [5].

Bollen et al [17] in their pilot study compared standard periodontal treatment comprising multiple sessions of SRP with FMD in patients with chronic periodontitis. Intensive scaling, subgingival irrigation, and tongue brushing using 1% chlorhexidine gel and 0.2% chlorhexidine rinses within 24 hours were carried out in the test group and simply SRP in the control group, followed by oral hygiene instructions to both groups. Plaque samples showed a greater reduction of harmful bacteria in the test group, especially around multi-rooted teeth, lasting up to 8 months. Anaerobic microbial flora remained lower in the test group than in the control. A significant increase in beneficial microflora was observed in the test group up to 4 months. FMD showed superior short-term microbiological outcomes.

Stein et al [18] in their randomized clinical trial compared four treatment groups: quadrant scaling and root planing (Q-SRP), full-mouth scaling, FMD, and FMD with erythritol air-polishing (FMDAP). All methods resulted in a reduction in PD and gain in CAL, along with improvement in the values of Balance of Payments over the period of 6 months. The FMDAP group showed the greatest reduction in PD for both moderate and deep pockets compared to Q-SRP. FMD also performed better than Q-SRP in deep pockets, but not as well as FMDAP. Conclusively, all the full-mouth approaches were more time-efficient than Q-SRP, with FMDAP being most effective in terms of pocket closure, especially in single-rooted teeth.

Platelet concentrates have gained popularity in the field of periodontal regeneration due to their wide range of use. Along with having the advantage of being autologous, it resulted in enhanced soft and hard tissue healing and amplified regenerative potential with uncomplicated preparation techniques. Differences in the preparation protocol have led to variable results in the literature [19].

i-PRF is a second-generation platelet concentrate that has shown significant regenerative potential in the field of dentistry and medicine. i-PRF differs from traditional PRP in that it is prepared without the use of anticoagulants, enabling a sustained and gradual release of growth factors, such as platelet-derived growth factor, transforming growth factor-β, and vascular endothelial growth factor. This promotes enhanced cell proliferation, migration, angiogenesis, and tissue regeneration, leading to overall enhancement in clinical parameters [10].

Thamaraiselvan et al [20] in their randomized parallel arm clinical trial evaluated the clinical parameters, such as PI, PBI, PD, and CAL, along with microbiological assessment at baseline, 6 weeks, and 12 weeks in patients with periodontitis randomly allocated into 3 groups with group A receiving ciprofloxacin-loaded i-PRF after SRP, group B receiving local drug delivery with i-PRF, and group C receiving SRP alone. The results demonstrated greater improvements in clinical parameters and a reduction in the microbial load as compared to other groups. The study concluded that ciprofloxacin-loaded i-PRF is a promising, autologous, and biocompatible vehicle for local drug delivery, combining antimicrobial efficacy of ciprofloxacin with regenerative potential, favorable tissue integration capability of i-PRF and its liquid injectable form offering the additional advantage of being flowable at placement before slowly polymerizing to gel in situ, thus adapting well to periodontal pocket. anatomy and minimizing the chances of displacement, thereby enhancing periodontal healing outcomes beyond SRP alone.

Miron et al [12] stated the natural clotting tendency of i-PRF post injection and effective delivery in periodontal pockets due to its injectable form, where it can demonstrate superior outcomes in terms of reduction in pocket depth, periodontal regeneration, gain in CAL, wound healing, and gingival tissue thickening. It also exhibits antimicrobial and anti-inflammatory properties, modulating polarization of macrophages toward a pro-healing M2 phenotype.

In this study, we hypothesize that the incorporation of i-PRF as an adjunct to OS-FMD will result in superior improvements in clinical outcomes such as clinical attachment gain and PD reduction, along with decreased PI and PBI scores due to its regenerative and anti-inflammatory properties along with enhanced healing potential, beyond the antimicrobial benefits achieved with chlorhexidine in the standard OS-FMD protocol. In addition, the preparation of i-PRF is a cost-effective, clinically feasible, minimally invasive, autologous, chairside procedure that can be realistically integrated into routine clinical practice.

The outcomes of this study will throw light on the therapeutic efficacy of an adjunctive use of i-PRF to OS-FMD therapy. Current protocols available in the literature for OS-FMD in the management of periodontitis primarily recommend SRP with the use of antimicrobials such as chlorhexidine according to the standard protocol given by Quirynen and colleagues [21]. By incorporating i-PRF, our trial will explore a regenerative adjunct that could potentially enhance healing outcomes and reduce disease recurrence. Integrating such biologically based approaches into established frameworks may provide clinicians with a more comprehensive, evidence-supported strategy, bridging antimicrobial therapy with regenerative potential. We believe that by establishing strong clinical evidence first, our study will provide a sound basis for future research to explore microbiological and biochemical pathways in greater detail. We also highlight that while this trial focuses on systemically healthy patients, the protocol may serve as a foundation for future studies in more diverse populations, thereby broadening its clinical relevance. The overall findings of the study will provide a strong groundwork for broader and more mechanistic investigations in the future.

